### Outcomes

#### Overview

The GMFM-66 will be defined as the primary outcome measure of the present study. The COPM will be considered a key secondary outcome, while all remaining secondary outcomes will be treated as exploratory measures.

#### Primary Outcomes

##### RCT1: High-Dosage Intervention (2-Week Home vs On-Site Camp)

The primary outcome measure for RCT1 will be the change in GMFM-66 observed after the 2 weeks of HABIT-ILE@home vs the HABIT-ILE on-site camp (T1-T0). The GMFM-66 evaluates children’s gross motor function skills through a large spectrum of tasks ranging from lying and rolling to walking, running, and jumping [26]. Linear measures (% of the full-range scale expressed in logits; from 0% to 100%) will be used to quantify clinical changes. Higher percentage values represent better gross motor function skills. The GMFM-66 item set version will be used as its responsiveness, reliability, and validity have been demonstrated in children with CP, including infants and toddlers [27,28]. The GMFM-66 assessments will be video-recorded and blindly assessed by trained examiners after study completion.

##### RCT2: Low- to Moderate-Dosage Home Follow-Up Interventions (9-Week HABIT-ILE@home Follow-Up vs Nonspecific Follow-Up)

The primary outcome is the same but will correspond to the change in GMFM-66 observed over the 9-week home follow-up period (HABIT-ILE@home follow-up vs nonspecific follow-up), measured from the end of the 2-week intensive intervention to the end of follow-up (T2-T1).

### Secondary Outcomes (RCT1 and RCT2)

#### Body Structures and Functions (Assessed at T0, T1, and T2)

Brain structural integrity will be evaluated using 3T brain MRI scanners. Prior to the scan, children will be familiarized with the MRI procedures. During the scan, they will watch an age-appropriate movie of their choice, except during the functional MRI acquisition. Structural brain images will be obtained using high-resolution 3D T1-weighted magnetization-prepared rapid acquisition with gradient echo and high-resolution 3D T2-weighted fluid-attenuated inversion recovery. Diffusion MRI data will be collected using a multishell approach with 20 directions at b=1000 s/mm², 60 directions at b=3000 s/mm², and 8 nondiffusion-weighted images (b=0 s/mm²). The diffusion acquisition will be divided into 4 blocks (22 directions/block) to facilitate efficient rescanning in the event of motion artifacts. Half of the blocks will be reverse phase-encoded to aid in correcting residual distortions caused by susceptibility inhomogeneities. Functional MRI data will be collected using a block design with an active hand and passive foot-tapping task. To correct susceptibility-induced distortions, 2 gradient-recalled echo images (TE1/TE2: 4.92/7.38 ms) will be used to acquire a field map for functional data. The total scan duration will be less than 1 hour.

Self-esteem of participants will be measured using the Self-ESTEEM-Kids-CP questionnaire [29]. This self-reported questionnaire covers various fields of self-esteem (global self-esteem, social acceptance, family relationship, friendship, scholastic competence, athletic competence, physical appearance, and behavior) and is illustrated in a comic strip-type format to make the assessment more fun and comprehensible for children. This tool, which is still under development, shows promising psychometric properties as reported in a preliminary study [29]. The linear measures are expressed as percentages of the full-range scale in logits, from 0% (low self-esteem) to 100% (high self-esteem).

Stereognosis will be assessed by the Improved Manual Form Perception Test [30,31], consisting of the tactile identification of concealed objects with one hand. Participants are required to identify the object as quickly as possible, either verbally or by pointing to the corresponding image on a standardized chart displaying multiple shapes. Both response time and the number of accurately identified objects will be recorded. It is reliable for school-aged children (aged 5‐18 years).

#### Activities (Assessed at T0, T1, and T2)

Bimanual performance will be assessed using the BoHA. It is a videotaped tool measuring how children with bilateral CP use both hands in bimanual activities. This tool also offers the opportunity to calculate an upper extremity asymmetry index. BoHA was validated for children with bilateral CP aged 18 months to 13 years [32]. For adolescents aged 14-18 years, the Adult Assisting Hand Assessment (Ad-AHA) can be administered using various bimanual activities, including a board game called Go with the Floe, which was the approach used in our study [33].

Unilateral gross manual dexterity of both hands will be evaluated by the Box and Block Test. This tool measures the number of blocks transported from one box to another in 1 minute. It is a valid and reliable test for children with mild to moderate bilateral manual ability impairments [34-36].

Unimanual dexterity in functional tasks will be measured using the Jebsen-Taylor Hand Function Test. This test records the speed required to perform 6 simulated everyday activities (turning over cards, picking up small objects, simulated eating, stacking checker pieces, and moving empty and full cans). The Jebsen-Taylor Hand Function Test is a valid test for children with mild to moderate unilateral manual ability impairments [37].

Manual performance, defined as the ability to manage daily activities requiring the use of the upper extremities (regardless of the strategies involved), will be measured with the ABILHAND-Kids questionnaire. Caregivers are asked to report on their child’s ease or difficulty in performing 21 manual activities. As a Rasch-built questionnaire, the linear measures correspond to the percentage of the full-range scale expressed in logits, from 0% (low manual performance) to 100% (high manual performance). ABILHAND-Kids is valid, reliable, unidimensional, and sensitive to change for children with CP [38,39].

Walk endurance will be evaluated by the 6-minute walk test. Participants are required to walk as far as possible along a 30-minute minimally trafficked corridor for a period of 6 minutes, with the measure being the 6-minute walk distance measured in meters. The 6-minute walk test is a reliable, reproducible, and valid tool for young ambulant people with CP [40-42].

Locomotor performance, defined as the child’s ability to move about effectively in the environment, will be measured by the ABILOCO-Kids questionnaire. Caregivers are asked to report on their child’s ease or difficulty in performing 10 locomotor activities. As a Rasch-built questionnaire, the linear measures correspond to percentages of the full-range scale expressed in logits, from 0% (low locomotor performance) to 100% (high locomotor performance). ABILOCO-Kids has been validated in children with CP [43].

Global activity performance, defined as the ability to manage daily activities requiring the use of the upper and/or lower extremities (regardless of the strategies involved), will be assessed by the ACTIVLIM-CP questionnaire. Caregivers are asked to report on their child’s ease or difficulty in performing 43 daily activities. As a Rasch-built questionnaire, the linear measures correspond to the percentage of the full-range scale expressed in logits, from 0% (low global performance) to 100% (high global performance). ACTIVLIM-CP is valid, reliable, unidimensional, and sensitive to change for children with CP [44,45].

Overall functional activity performance will be measured by the four domains of the Pediatric Evaluation of Disability Inventory–Computer Adaptive Test (PEDI-CAT): daily activities, mobility, social and cognitive activities, and responsibility. The PEDI-CAT includes a comprehensive item bank of 276 functional activities. A computer adaptive testing methodology is used to administer the tool by selecting the items that are most appropriate for children’s levels and minimizing the number of items required to ensure an accurate measure. The PEDI-CAT is designed for use with children and youth (birth through 20 years of age) with a variety of physical and/or behavioral conditions [46]. As a Rasch-built questionnaire, the linear measures correspond to the percentage of the full-range scale expressed in logits, from 0% (low manual performance) to 100% (high manual performance).

The children’s performance perceived by caregivers on functional goals and their satisfaction with the achieved performance will be quantified using the COPM [47]. Caregivers are asked to estimate their child’s performance and their satisfaction on a 10-point scale, from 1 (low performance or satisfaction) to 10 (high performance or satisfaction).

#### Participation

Participation, defined as children’s involvement in life situations (chosen because they make sense to them) in which they interact with others or which are linked to social roles, will be measured by the Participation In Life Situations–Kids–CP questionnaire. This self-reported questionnaire covers various domains of participation such as moving around in different places, recreation and leisure, school education, family relationships, interpersonal interaction, or problem solving. The life situations in the questionnaire are illustrated in a comic strip-type format to make the assessment more fun and comprehensible for children. This tool, which is still under development, will generate linear measures (percentage of the full-range scale expressed in logits), from 0% (low participation) to 100% (high participation).

#### Satisfaction Questionnaire (Feasibility and Adherence to Treatment)

A satisfaction questionnaire was developed to evaluate the feasibility of HABIT-ILE@home and compare it with the HABIT-ILE on-site method. Children’s and caregivers’ adherence to treatment will also be recorded and compared between both methods through the satisfaction questionnaire. The questionnaire will include items related to therapy burden, perceived feasibility, adherence, and acceptability of the intervention. It will be filled out by children, caregivers, and/or interventionists after the 2-week high-dosage intervention (T1) or after the 9-week home follow-up (T2).

#### Quantification and Qualification of Movements

The quantity and type of upper and lower extremity movements achieved during the 2-week interventions will be recorded using 3 accelerometers (2 placed on the dorsal side of the wrists and 1 on the upper side of the thigh, approximately in the middle of the thigh segment) to verify equivalence in therapy content between groups (2-wk HABIT-ILE@home vs HABIT-ILE on-site camp, RCT1). The Xsens DOT sensors will provide accurate measurements of accelerations and orientations, with demonstrated fair to excellent validity and reliability [48]. Triaxial acceleration data will be recorded over the 6.5 hours of daily therapy at a sampling frequency of 30 Hz. These data will be analyzed to yield an activity count (based on a predefined threshold for movement), an asymmetry ratio (comparing right and left upper extremity activity), and lower extremities activity positions (reflecting the percentage of time spent sitting, standing, or walking). These Inertial Measurement Unit (IMU) data will provide an objective measure of motor engagement and therapy intensity during the intervention.

### Statistical Analysis

#### Overview

Statistical analyses will be conducted following the collection of final measurements taken at the follow-up assessment. This will be conducted using SPSS software (IBM Corp; version 29.0.1.0), with a significance level set at *α*=.05.

All analyses will be conducted using an intention-to-treat approach, and missing data will be handled using multiple imputation methods.

Variables used for pairing (age, MACS, and GMFCS) were used to ensure baseline comparability between groups. Baseline characteristics, including sex, age, MACS, GMFCS, living area (urban or rural), type of housing, number of siblings, baseline outcome measures, and the type and amount of usual paramedical care (eg, physical therapy, occupational therapy, and psychomotor therapy) will be compared between groups to assess initial comparability using appropriate statistical tests (eg, Mann-Whitney rank sum test for continuous variables and Cochran-Armitage test for ordinal variables).

#### RCT1: High-Dosage Intervention (2-Week Home vs On-Site Camp)

Changes within each intervention group between baseline and post intervention (T1-T0) will first be assessed. Paired-sample *t* tests will be used when data are normally distributed, while the nonparametric Wilcoxon signed-rank test will be applied in the case of nonnormal distributions.

Noninferiority analyses will be performed by comparing changes obtained between groups (mean change in the HABIT-ILE@home group minus the HABIT-ILE on-site group). The mean obtained difference and its 95% CI will be compared to the prespecified NIM. The NIM has been set for each outcome measure based on the MCID.

For normally distributed data, the between-group difference and its CI will be estimated using an independent samples *t* test (or Welch *t*-test when variances are unequal). When the assumption of normality is not verified, Mann-Whitney *U* tests will be applied.

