### Sample Size

#### RCT1: High-Dosage Intervention (2-Week Home vs On-Site Camp)

Sample size calculation was performed using PASS (version 14.0.15; NCSS) for a one-sided noninferiority *t* test comparing 2 independent means. The analysis was based on the mean improvement in GMFM-66 observed in the study of Bleyenheuft et al [7]. We hypothesized that there would be a true difference of Gross Motor Function Measure (GMFM) units between groups, with an α of .05 and a 1-*β* of 0.9. We estimate that the noninferiority margin (NIM) could reach a maximum of 2 GMFM units since this value is the minimal clinically important difference (MCID) of the GMFM-66. The data are drawn from populations with SDs of 1.9 GMFM units. Consequently, 17 participants are needed per group (N=34). Considering 25% potential dropouts per group, 44 participants will be included.

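### RCT1 is sized for a one-sided 5% test but judged on a 95% CI; under that rule 17 per group give about 84% power, not 90%

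*Protocol article*

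**What the plan says.** All references are to the protocol article.

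- **Sample Size, RCT1.** The calculation is "for a one-sided noninferiority *t* test comparing 2 independent means", "with an α of .05 and a 1-*β* of 0.9". On the margin, the text says "the noninferiority margin (NIM) could reach a maximum of 2 GMFM units", and on variability, "The data are drawn from populations with SDs of 1.9 GMFM units". The assumed true difference has no number: "We hypothesized that there would be a true difference of Gross Motor Function Measure (GMFM) units between groups". The result is "Consequently, 17 participants are needed per group (N=34). Considering 25% potential dropouts per group, 44 participants will be included".
- **Statistical Analysis, RCT1.** Noninferiority is decided on the change T1-T0, home minus on-site: "The mean obtained difference and its 95% CI will be compared to the prespecified NIM". For normally distributed data, the difference and its interval come from an independent-samples t test, or Welch's version if variances differ.
- **Statistical Analysis, Overview.** The significance level is .05, with no statement of one or two sides.

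The article nowhere mentions a 90% interval or a one-sided confidence bound.

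**The concern.** In a noninferiority trial the confidence level is the decision rule. The lower limit of a two-sided 95% CI lies above -2 exactly when a one-sided 2.5% test rejects. The one-sided 5% test used for sizing corresponds to a two-sided 90% CI. The protocol therefore appears to fix two error rates for one primary decision, and the 90% power belongs to the rule that will not be applied.

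Two things are at stake. If noninferiority is missed, a reader relying on the Sample Size section will put the chance of missing a truly equivalent home programme at 10%, when at the planned number of evaluable children it is higher. There is also a band of observed differences in which the verdict depends on which section is followed.

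**Working it through.** **Inputs** (Sample Size, RCT1, unless noted)

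- Margin M = 2 and SD = 1.9 GMFM-66 units
- One-sided alpha .05, target power 0.90
- 17 evaluable per group, 25% dropout, 44 enrolled (22 per group, Study Design)
- True difference d: no number in the text. I take d = 0, which reproduces the stated n.
- Decision rule: 95% CI against the margin (Statistical Analysis, RCT1), so one-sided alpha .025 on the two-sided reading

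**Formula.** For n per group, SE = SD × √(2/n), df = 2n - 2, noncentrality = (M - d)/SE. Power = P(T > t_crit), where T is noncentral t with these df and noncentrality, and t_crit is the central t quantile at 1 - alpha.

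**Step 1: the protocol's own figure.** At n = 17, SE = 1.9 × √(2/17) = 0.652, noncentrality = 2/0.652 = 3.07, df = 32. At one-sided .05, t_crit = 1.694 and power is 91.3%. At n = 16 power is 89.7%. So 17 is the smallest n reaching 90%, as stated.

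**Step 2: the written decision rule.** With the same inputs at one-sided .025, t_crit = 2.037 and power at n = 17 is 84.5%. The type II error is 15.5% instead of 10%.

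| Evaluable per group | Power, one-sided .05 | Power, one-sided .025 (95% CI rule) |
|---|---|---|
| 16 | 89.7% | 82.1% |
| 17 | 91.3% | 84.5% |
| 19 | 93.8% | 88.4% |
| 20 | 94.8% | 90.0% |
| 21 | 95.6% | 91.4% |
| 22 | 96.3% | 92.7% |

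The 95% CI rule needs 20 evaluable per group for 90%. The normal approximation gives the same picture: 86.6% at 17, and 19 per group for 90%.

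**Step 3: dropout.** 17 × 1.25 = 21.25, rounded up to 22 per group, matches the 44 enrolled. To keep 17 after losing 25%, one divides: 17/0.75 = 22.7, so 23 per group and 46 in total. Conversely, 44 × 0.75 = 33 completers, not 34. With 16 and 17 per group, power is 83.3% under the 95% CI rule and 90.5% under the one-sided 5% rule.

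**Step 4: where the verdict would differ.** Noninferiority is shown when the observed difference exceeds -2 + t_crit × SE, taking the observed SD as 1.9.

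- 17 per group: one-sided 5%: -2 + 1.694 × 0.652 = -0.90. 95% CI: -2 + 2.037 × 0.652 = -0.67.
- 22 per group (SE = 0.573): -2 + 1.682 × 0.573 = -1.04, and -2 + 2.018 × 0.573 = -0.84.

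An observed difference between -0.90 and -0.67 (17 per group), or between -1.04 and -0.84 (22 per group), passes one rule and fails the other.

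**Step 5: sensitivity to the missing true difference.** A true deficit of 0.1 in the home group would need 18 per group at one-sided .05 and 23 at .025. A deficit of 0.25 would need 21 and 26. Neither gives 17 under either rule. With a deficit of 0.25, 17 per group have 74% power under the 95% CI rule.

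**The case against.** The strongest reply is that the protocol never says two-sided. If its 95% CI means a one-sided 95% bound, sizing and analysis agree and no power is lost. That reading is possible, but an unqualified CI from a t test is conventionally two-sided and nothing in the article points the other way. Even on this reading the text has to say so.

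Second, 84.5% is not the power of the trial as enrolled. With 22 per group the 95% CI rule has 92.7%, and the stated 90% survives two losses per group. Missing data are also to be multiply imputed, so the primary analysis is not a pure completer analysis. This stands as a limit on the consequence: at full retention the chance of missing a truly equivalent programme is 7.3%, below the stated 10%. It does not rescue the stated figure, which the protocol ties to 17 evaluable per group, and imputation does not restore all the lost information.

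Third, the mismatch is conservative. A 95% CI holds the risk of a false noninferiority claim at 2.5%, not 5%. That is correct, and it is why the 95% rule is the one to keep.

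Fourth, the dropout slip is one child, the method of inflation is inferred from the result, and under the protocol's own sizing rule 33 completers still give 90.5%. It is a secondary correction.

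That the confidence level might be chosen after seeing the data is conjecture: the analysis section names one level, 95%.

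**Conclusion.** The concern holds. The sample size of 17 per group is arithmetically right for a one-sided 5% test, but the protocol decides noninferiority on a 95% CI. Under that rule 17 per group give 84.5% power, about 5.5 points below the stated 90%, and 20 per group would be needed. For the 44 enrolled, power ranges from about 83% after the planned 25% loss to 92.7% with none.

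These figures rest on three assumptions: the interval is two-sided, the true difference is 0 (the document gives no number), and the SD is 1.9. A true deficit in the home group would lower the power further. The type I error is not inflated.

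**What to change.** Use one alpha level in both sections. The better choice is to keep the 95% CI, because it is already the written decision rule and because relaxing it after data collection would be hard to defend.

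- **Statistical Analysis, RCT1:** state that the CI is two-sided and that noninferiority is concluded if its lower limit (home minus on-site) lies above -2 GMFM-66 units for the primary outcome.
- **Sample Size, RCT1:** state that the calculation used one-sided 5%; that under the 95% CI rule (one-sided 2.5%) 17 per group give 84% power and 20 would be needed for 90%; and that the 44 enrolled give 83% after 25% loss and 93% with none. Supply the missing true difference; these figures assume 0.
- **Dropout:** correct the inflation to n/(1 - 0.25), and say that 25% loss from 44 leaves 33 children. This restates the expected completers and is not a call to enrol more.

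If a one-sided 95% bound (a two-sided 90% CI) was the intended rule from the start, saying so would also reconcile the sections, but it should be supported by a document dated before the data were seen. The article reports the analysis as completed in May 2025 and the results as not yet submitted, so the level should be declared before publication.

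The cost is a few sentences and a less favourable stated power. No new children and no new data are required.

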### Randomization Process

At the end of the recruitment phase, children were paired by the investigators according to Manual Ability Classification System (MACS) level, Gross Motor Function Classification System (GMFCS) level, and age, in this order of priority. Within each pair, participants were randomly assigned a code number (1 or 2) using Research Randomizer. To ensure allocation concealment and limit selection bias, the correspondence between the code number and the intervention group was determined independently by a person from an affiliated laboratory who was not involved in recruitment, assessment, or intervention delivery. This person indicated whether code 1 corresponded to the control group or to the treatment group after the pairs and code numbers had been generated. For RCT2, participants within each group of RCT1 were randomized again according to the same procedure to either the HABIT-ILE@home follow-up or the nonspecific home follow-up group (Figure 1).

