#### RCT2: Low- to Moderate-Dosage Home Follow-Up Interventions (9-Weeks HABIT-ILE@home Follow-Up vs Nonspecific Home Follow-Up)

Changes within each group during follow-up (T2-T1) will be assessed using paired-sample *t* tests when data are normally distributed, or Wilcoxon signed-rank tests in the case of nonnormal distributions.

The superiority analysis will be based on between-group comparisons using an analysis of covariance (ANCOVA) model. For each outcome, the model will be specified as outcome at T2 ~ outcome at T1 + RCT1_group × RCT2_group. This model will include the baseline value at T1 as a covariate and will test the main effects of the initial intervention (HABIT-ILE@home vs on-site), the follow-up intervention (HABIT-ILE@home follow-up vs nonspecific home follow-up), and their interaction. This approach will allow the effect of the second randomization (RCT2) to be evaluated while accounting for the initial allocation in RCT1.

The inference for superiority will be based on the main effect of RCT2_group (HABIT-ILE@home follow-up vs nonspecific home follow-up), adjusted for T1 values and RCT1_group. The interaction term (RCT1_group × RCT2_group) will be examined to explore whether the effect of the follow-up intervention differs depending on the initial intervention.

For normally distributed outcomes, model assumptions will be checked and standard ANCOVA estimates will be used. If normality is not verified, a nonparametric alternative based on rank-transformed ANCOVA will be applied.

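### RCT1's non-inferiority interval uses neither the matched pairs from the randomisation nor baseline GMFM-66 as a covariate; the cost is a possibly conservative interval and a modest loss of power

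*Protocol article*

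**What the plan says.** - **Randomization Process:** "children were paired by the investigators according to Manual Ability Classification System (MACS) level, Gross Motor Function Classification System (GMFCS) level, and age", in that order of priority. Allocation is one to one inside the pair: "Within each pair, participants were randomly assigned a code number (1 or 2) using Research Randomizer". The second randomisation, within each RCT1 group, follows the same procedure.
- **Sample Size, RCT1:** sized for a "one-sided noninferiority *t* test comparing 2 independent means", "with an α of .05 and a 1-*β* of 0.9", margin 2, SD 1.9, giving 17 evaluable per group and 44 enrolled.
- **Statistical Analysis, Overview:** "Variables used for pairing (age, MACS, and GMFCS) were used to ensure baseline comparability between groups". No model term is named for them.
- **Statistical Analysis, RCT1:** "Noninferiority analyses will be performed by comparing changes obtained between groups", home minus on-site, with the 95% CI set against the margin. "For normally distributed data, the between-group difference and its CI will be estimated using an independent samples" t test, or Welch. Mann-Whitney is the fallback if the data are not normal.
- **Statistical Analysis, RCT2:** an ANCOVA of the T2 value. "This model will include the baseline value at T1 as a covariate". The matching factors are not in this model either.

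**The concern.** Matching on prognostic factors is meant to make the two children in a pair alike. If their changes are alike too, the difference between arms varies less than it would under simple randomisation. An independent-samples standard error does not credit that, so it is too large. The non-inferiority decision depends on where the lower confidence limit falls relative to -2, so an oversized standard error makes non-inferiority harder to show.

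The article is also inconsistent with itself. It adjusts for the starting GMFM-66 in RCT2 but not in RCT1, and gives no reason. The RCT1 test is stated outright, so this is not a detail left to a fuller document.

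**Working it through.** **Inputs.** From the Sample Size section: margin 2, SD 1.9 (taken as the SD of change; the text does not say), 17 evaluable per group, one-sided alpha 0.05, power 0.90. From Study Design: 22 per group, hence 22 pairs if all 44 children are paired and complete. The text as read shows no number for the true difference, so 0 is assumed. The document gives neither the within-pair correlation of change (rho) nor the share of variance in change that covariates explain (R²); both are varied.

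**1. The plan's own figure.** For an unpaired t test, SE = 1.9 × √(2/17) = 0.652 and the noncentrality is 2/0.652 = 3.07. With 32 df and one-sided 0.05, power is 0.913; at 16 per group it is 0.897. So 17 reproduces, and it reproduces as an unpaired design.

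**2. Effect of pairing on the planned interval.** The true variance of the difference is 2σ²(1-rho)/n, while the planned test estimates about 2σ²/n. The effective critical value is therefore t/√(1-rho). With 22 pairs (42 df, t = 2.018):
- rho 0.1: 2.018/√0.9 = 2.13, so coverage is about 0.96.
- rho 0.3: 2.018/√0.7 = 2.41, so coverage is about 0.98.

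Simulation at 22 pairs agrees:

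| rho | Coverage | One-sided error at the margin |
|---|---|---|
| 0 | 0.951 | 0.024 |
| 0.1 | 0.962 | 0.019 |
| 0.3 | 0.979 | 0.010 |

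At 17 pairs the simulated one-sided error is 0.020, 0.015 and about 0.010 for rho 0.1, 0.2 and 0.3.

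**3. Interval width.** Half-width at 22 per group:
- Planned: 2.018 × 1.9 × √(2/22) = 1.156.
- Strict paired t test (21 df, t = 2.080): 1.191 at rho 0, 1.130 at 0.1, 0.997 at 0.3.
- Break-even: rho = 1 - (2.018/2.080)², about 0.06. At 17 pairs it is 1 - (2.037/2.120)², about 0.08.

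**4. Power under the 95% CI rule** (planned test simulated, paired test from the noncentral t):

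| rho | 22 pairs: planned | 22 pairs: paired | 17 pairs: planned | 17 pairs: paired |
|---|---|---|---|---|
| 0 | 0.927 | 0.914 | 0.845 | 0.821 |
| 0.1 | 0.937 | 0.939 | 0.856 | 0.859 |
| 0.3 | 0.957 | 0.978 | 0.884 | 0.931 |

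The planned test's power itself rises with rho, because balanced allocation helps the estimate whatever the analysis. Comparing adjusted power with 0.845 throughout would overstate the gain.

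**5. The ANCOVA with four covariates at 17 per group.** Simulated with equal contributions from T0 GMFM-66, GMFCS, MACS and age, and the last three perfectly matched: power is about 0.83 at R² = 0, 0.87 at 0.1 and 0.94 at 0.3. In that setting rho = 0.75 × R², that is 0.075 and 0.225 for the last two. Interpolating in the simulated values at 17 pairs (including 0.871 at rho 0.2) puts the planned test at about 0.85 and 0.87. The gain is then about 1 to 2 points at R² = 0.1 and about 6 at 0.3. If dropout leaves all four covariates only randomly balanced, power is about 0.79 at R² = 0, 0.83 at 0.1 and 0.91 at 0.3.

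**The case against.** The strongest reply is that the plan is coherent and errs on the safe side. RCT1 is both sized and analysed as two independent means, and any miscalibration is conservative. At the enrolled size the loss is at most about two points for rho up to 0.3, from a base above 92%. Replacing the primary model after the analysis is finished would be post hoc. Each of these statements is right, and together they limit the point to an improvement.

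Four stronger readings are tempting, and the document does not support them:
- **The baseline is ignored.** It is not: the outcome is change, which subtracts it. What is missing is covariate adjustment, so an imbalance in starting GMFM-66 matters only as far as baseline predicts change. Matching on GMFCS should limit that further.
- **The interval is certainly too wide.** That depends on a correlation the article does not give. At zero correlation the planned interval is correct and a strict paired test is slightly worse.
- **A false claim of non-inferiority becomes more likely.** With positive correlation the one-sided error falls below 2.5%.
- **RCT2 is deficient for leaving out the matching factors.** That model already adjusts for the T1 value, and no gain from adding them has been shown.

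What the reply does not remove is the mismatch between a matched allocation and an analysis that makes no use of it, or the unexplained difference between RCT1 and RCT2.

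**Conclusion.** The mismatch is established from the text; its size is conditional. For an assumed within-pair correlation of 0.1 to 0.3, SD of change 1.9 and true difference 0, the planned 95% CI covers about 96% to 98%, and one-sided error is about 2.0% to 1.0%. Relative to a paired analysis, the power forgone is about 0 to 2 points with 22 complete pairs and about 0 to 5 points with 17. At zero correlation there is no loss.

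This is worth changing, but a positive non-inferiority result from the planned test would not be undermined by it. A separate matter costs more at the planned evaluable size: sizing uses one-sided 0.05 while the decision uses a 95% CI. If that CI is two-sided, power at 17 per group is 0.845 (at zero correlation) and 20 per group would be needed for 0.90. That shortfall should not be attributed to the pairing.

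**What to change.** Make the RCT1 between-group analysis an ANCOVA: T1 GMFM-66 on T0 GMFM-66, group, GMFCS, MACS and age, with GMFCS and MACS as linear scores. Compare the adjusted home-minus-on-site difference and its CI with -2. Unlike a strict paired t test, this keeps a child whose partner drops out. Keep the unadjusted t test, and a model with pair as a random effect, as sensitivity analyses.

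The Results section says data analysis was completed in May 2025. The ANCOVA must therefore be labelled as added after the protocol and reported beside the planned t test, whichever way the two fall.

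Cost: no new data and four degrees of freedom. If the covariates explain nothing, power at 17 per group is about 83% against 84.5% while the matching factors stay balanced, and about 79% if dropout leaves them only randomly balanced. Adding the matching factors to the RCT2 model is optional.
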